### Blinding

Due to the nature of the intervention blinding of participants, SFP10-14 facilitators and data collectors is not possible.

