**Methods/Design:**

A cluster randomized controlled trial in community settings across Poland. Communities will be randomized to a SFP10-14 trial arm or to a control arm. Recruitment and consent of families, and delivery of the SFP10-14, will be undertaken by community workers. The primary outcomes are alcohol and other drug use and misuse. Secondary (or intermediate) outcomes include parenting practices, parent–child relations, and child problem behaviour. Interview-based questionnaires will be administered at baseline, 12 and 24 months.

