### Intervention

The SFP10–14 is a video based programme delivered by trained facilitators that includes parents/guardians and children learning together [26-29]. The 7-week program is delivered over 7-sessions, with 4 optional booster sessions available several months later. The weekly sessions last two to three hours: in the first hour parallel groups of children and parents from up to 15 families develop their understanding and skills, led by parent and child group facilitators; in the second hour, parents and children come together in family units to practice the principles they have learned. The remaining time is spent in logistics, meals and enjoyable family activities. The programme is highly structured with detailed manuals, videos and activities whilst at the same time being highly interactive [26-29].

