#### Primary outcomes

· Alcohol, cigarette and other drugs: age of first use, lifetime prevalence, 30-days (not other drugs) and 12-month prevalence

· Alcohol use without parent permission

· Drunkenness/binge drinking in past 30 days

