### Data collection

Data are collected at baseline, 12 and 24 months. Interview-based questionnaires will be completed by parents and independently by children in separate rooms. In the control group one parent (or both if they express an interest) will complete the questionnaire, and if there are two children in the target age range (10–14) only the youngest will be asked to complete the questionnaire.

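### The nature of the intervention does not explain why data collectors cannot be blinded, and the substance-use outcomes come from interview-based questionnaires with no stated safeguard against arm-aware interviewers

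*Protocol article*

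**What the plan says.** The Blinding section is one sentence, which says that because of the nature of the intervention "blinding of participants, SFP10-14 facilitators and data collectors is not possible". It gives no other reason.

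The Intervention section describes what that nature is: "The SFP10–14 is a video based programme delivered by trained facilitators that includes parents/guardians and children learning together". The Methods paragraph of the Abstract adds who does the work: "Recruitment and consent of families, and delivery of the SFP10-14, will be undertaken by community workers". Neither place mentions data collectors.

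Under Data collection, "Data are collected at baseline, 12 and 24 months", and "Interview-based questionnaires will be completed by parents and independently by children in separate rooms". The same section then sets a rule, for control families only, on how many parents and which child complete the questionnaire.

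The primary outcomes are substance use throughout: "Alcohol, cigarette and other drugs: age of first use, lifetime prevalence, 30-days (not other drugs) and 12-month prevalence", alcohol use without a parent's permission, and "Drunkenness/binge drinking in past 30 days". No objective measure of use is listed.

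**The concern.** A group programme for families cannot be hidden from those who attend it or lead it. Whether the person administering a questionnaire at 12 or 24 months knows the community's allocation is a separate matter, which depends on how the fieldwork is organised. By calling masking impossible for all three groups on one ground, the protocol closes off a protection that could at least be attempted.

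It matters here because minors are being asked about drinking, smoking and drug use. A child from a programme family may be less willing to admit use than a control child, and an interviewer known to be aware of the arm, or who words or probes questions differently, may widen that gap. Lower reporting in the intervention arm cannot be told apart from lower use. The analyses planned under Analyses (multi-level modelling, intention to treat, multiple imputation) deal with clustering, non-adherence and missing data. None of them corrects answers that differ by arm because of how they were obtained.

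**Working it through.** The article states no figure that depends on blinding, so there is nothing to reproduce. The check is first a reading of the sections together, then an illustration.

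**Does the reason support the conclusion?**

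| Group | Part in SFP10-14 according to the article | Does the stated reason cover them? |
|---|---|---|
| Participants | Attend the sessions (Intervention) | Yes |
| Facilitators | Lead the sessions (Intervention) | Yes |
| Data collectors | None described (Abstract, Intervention, Data collection) | No |

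**Does the mode of collection leave room for influence?** The questionnaires are interview-based. The article does not say whether the child writes the answers or gives them to the interviewer. Separate rooms shield the child's answers from the parent, not from the interviewer. That the outcomes are the child's own report is an inference from the Primary outcomes and Data collection sections; no informant is named.

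**How large could differential reporting be?** The article gives no reporting rates, so these values are assumed: true prevalence 30% in both arms (no programme effect), with 90% of users reporting in control.

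- Control: 0.30 × 0.90 = 27%
- Intervention, 80% of users reporting: 0.30 × 0.80 = 24%, a spurious difference of 3 points
- Intervention, 70% of users reporting: 0.30 × 0.70 = 21%, a spurious difference of 6 points

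**What would that do to a test?** Inputs: 600 families (Sample size calculation) and 1:1 allocation of communities (Design), taken as 300 families per arm without attrition. Prevalence is 10% and 53%, the proportions ever drunk at ages 11 and 15 (Background), plus the assumed 30%. The design effect is assumed to be 1, 1.5 or 2. For simplicity control reporting is complete, and the intervention arm under-reports by a relative amount u.

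- p₂ = p(1 − u); d = p − p₂; p̄ = (p + p₂)/2; n = 300/design effect
- se₀ = √[2p̄(1 − p̄)/n]; se₁ = √{[p(1 − p) + p₂(1 − p₂)]/n}
- False-positive rate = Φ[(d − 1.96 se₀)/se₁] + Φ[(−d − 1.96 se₀)/se₁]

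Example with p = 0.30, u = 0.10 and design effect 1: p₂ = 0.27, d = 0.03, se₀ = 0.0369, se₁ = 0.0368, giving 12.9%.

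| True prevalence | u | Spurious difference (points) | False-positive rate, design effect 1 / 1.5 / 2 |
|---|---|---|---|
| 10% | 10% | 1.0 | 7.0% / 6.3% / 6.0% |
| 10% | 20% | 2.0 | 13.7% / 10.7% / 9.3% |
| 30% | 10% | 3.0 | 12.9% / 10.2% / 8.9% |
| 30% | 20% | 6.0 | 38.0% / 27.1% / 21.5% |
| 53% | 10% | 5.3 | 25.4% / 18.5% / 15.0% |
| 53% | 20% | 10.6 | 74.0% / 56.5% / 45.1% |

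With u = 0 the rate is 5.0% in every case. All of these results describe total differential reporting from any cause. How much of it would come from interviewers knowing the arm cannot be worked out from the article.

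**The case against.** The case for the protocol has four parts.

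- **The child's own knowledge is probably the main route.** Participants cannot be blinded, so a masked interviewer would still hear answers shaped by having attended. This stands: masking would reduce the bias, not remove it.
- **Masking may fail in practice.** Whole communities are allocated, the programme is visible, families may mention it, and the control-only questionnaire rule could itself reveal the arm. This also stands, but the article does not give these as its reason, and difficult is not impossible.
- **The lack of blinding is openly disclosed.** True. Simply striking data collectors from the sentence could make the document less candid if they still learn the arm, so the correction must keep the disclosure.
- **A condensed article leaves interviewing detail to fuller documents.** Fair, and silence on how items are administered is no fault in itself. The point rests on an affirmative statement whose reason does not support it.

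A reader might infer three stronger things, and the article supports none of them. One is that the community workers who recruit and deliver also collect the data; the article does not say who the data collectors are. Another is that every primary outcome will be biased in favour of SFP10-14; direction and extent are assumptions. The third is that 3 to 6 points is the avoidable bias; those figures do not isolate the interviewer's share.

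**Conclusion.** The point holds in a limited form. The stated reason covers participants and facilitators only, and the claim that data collectors cannot be blinded is left without support. Since the primary outcomes come from interview-based questionnaires, arm-aware interviewers may add to differential reporting. A direction favouring the programme is plausible, not established.

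The size is not derivable from the documents. Under the assumed values, total differential reporting of 3 or 6 points at 30% prevalence would raise the false-positive rate from 5.0% to 8.9–12.9% or 21.5–38.0% (complete reporting in control, 300 families per arm, design effect 1 to 2). The interviewer's contribution is some unknown part of that. The change should be made, because a cheap safeguard exists that helps even where masking fails. The point does not by itself invalidate the trial.

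**What to change.** 1. In Blinding, limit the impossibility statement to participants and facilitators. State that data collectors will not be told the allocation where feasible, that any unmasking will be recorded, and that it will be disclosed as a limitation.
2. In Data collection, have children in both arms complete the substance-use items privately at every wave and seal them under a study number before handing them over. This protects the answers even when the interviewer knows the arm.
3. Where existing staffing allows, do not use anyone who recruits for or delivers SFP10-14 in a community as a data collector there.
4. Replace the control-only rule on who completes the questionnaire with one rule for both arms.
5. If figures such as 3 and 6 points are quoted, label them as total differential reporting under assumed values.

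Cost: revised data-collection instructions, some rescheduling, and slightly more missing items in the self-completed section. Item 3 is conditional because the article does not describe the fieldwork staff; none of the steps requires an additional assessor.

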### Sample size calculation

No formal sample size calculation was undertaken but funding was requested for a sample size (N = 600 families) which was similar to that reported in other trials of the SFP10-14 [12-16]. These other trials have reported SFP10-14 effectiveness for reducing a number of risky behaviours amongst young people, including alcohol and drug use and misuse and other behavioural problems.

### Analyses

Clustering at the community and family level will be taken account of in multi-level data analysis. Statistical tests of difference in proportions or mean difference tests (or non-parametric equivalents) will be used to examine differences between intervention and control groups. Based on pilot study results [40], data will be analyzed for the whole sample and by several sub-group analyses: child age group (10–12; 13–14); family problems (violence, chronic illness, substance use problems, financial problems etc.; low vs high severity); child behaviour and emotional problems (low vs high severity). All analyses will be on an intent-to-treat basis, and both completed case analysis and multiple imputation analysis will be undertaken.

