## Background

The European Union (EU) is the heaviest drinking region of the world, drinking 11 litres of pure alcohol per adult each year [1]. More than 1 in 4 deaths among men (aged 15–29 years) and 1 in every 10 deaths among young women in the EU is alcohol related [2]. Young people (aged 15–24 years) are responsible for a high proportion of this burden, with over 25% of youth male mortality and approximately 10% of young female mortality being due to alcohol [1]. Sparse information exists on the extent of social harm in young people, despite the fact that a third of a million (6%) 15–16 year old school students in the EU report engaging in fights, and 200,000 (4%) report unprotected sex, due to their own drinking [1].

Alcohol and other drug use increases markedly between the ages of 11 and 15 years amongst young people in Poland. Between the ages of 11 and 15 the proportion of those who have ever smoked increases from 12% to 59%. At age 11, 10% of 11-year-olds report that they have ever been drunk, and this increases to 53% amongst 15-year-olds. Moreover, 18% of Polish youth report lifetime cannabis use [3]. Early alcohol and other drug use is associated with a range of subsequent adverse health and social outcomes [4-11].

The Strengthening Families Program 10–14 (SFP10-14) is a US-developed family-based intervention for preventing alcohol and other drug use and problems amongst young people. It has been evaluated in two large-scale randomized controlled trials in Iowa, USA [12-16] and has informed the development of a family-based intervention for African American families evaluated in a large randomized controlled trial in rural Georgia, USA [17-19]. Several systematic reviews have highlighted the promising results from these trials but also note the question of whether this US-developed intervention will be applicable in other countries and settings [20-25].

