## Methods/Design

### Design

A parallel group cluster randomized controlled trial where communities will be randomly assigned, with concealed allocation, to one of two groups, with a 1:1 allocation ratio. Communities in the intervention arm will participate in SFP10-14 group sessions; communities in the control arm of the trial will receive information leaflets for families. All families recruited into the trial will be assessed at baseline and at 12 and 24 months follow-up. Two years after baseline data collection, families from control communities will be offered the opportunity to participate in SFP10-14.

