### Randomization

Randomization occurs after communities have consented to participate in the trial. Simple randomization of community to intervention or control arm will be undertaken by the lead investigator drawing names out of a hat in a concealed allocation format.

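### The Analyses section names two-sample tests for the arm comparison beside a promised multi-level analysis, does not reconcile the two, and names no adjustment for baseline outcome or child age

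*Protocol article*

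**What the plan says.** Only the protocol article is at hand. Its Analyses section opens with a commitment: "Clustering at the community and family level will be taken account of in multi-level data analysis". The next sentence gives the method for comparing the arms: "Statistical tests of difference in proportions or mean difference tests (or non-parametric equivalents) will be used to examine differences between intervention and control groups". Nothing links the two sentences or says which of them yields the primary result.

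Child age appears in this section only as a sub-group variable ("data will be analyzed for the whole sample and by several sub-group analyses: child age group", split at 10–12 and 13–14). Family problems and child behaviour or emotional problems are used in the same way. No covariate is named for the whole-sample comparison, and none is excluded.

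Four other parts of the article bear on the point:

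- Design makes the community the unit of allocation: "communities will be randomly assigned, with concealed allocation, to one of two groups, with a 1:1 allocation ratio".
- Randomization describes the method, with no stratification or matching: "Simple randomization of community to intervention or control arm will be undertaken by the lead investigator drawing names out of a hat".
- Data collection provides a baseline wave: "Data are collected at baseline, 12 and 24 months".
- Background shows how strongly one relevant behaviour depends on age: "At age 11, 10% of 11-year-olds report that they have ever been drunk, and this increases to 53% amongst 15-year-olds".

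**The concern.** Two-sample tests of proportions or means, and rank tests, treat children as independent when run in their ordinary form. In a trial that randomizes communities this makes standard errors too small, so whether the primary test is valid depends on which of the two sentences governs. Mention of a test of proportions or means could be shorthand for an arm contrast within a multi-level model. The non-parametric option fits that reading less well, because an ordinary rank test is an alternative to a model and not a contrast within one.

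The second issue remains even if clustering is handled. Lifetime prevalence and age of first use are among the primary outcomes, and both are cumulative: a child who had already used at baseline still counts at 24 months. A comparison that takes no account of baseline therefore carries any baseline difference between arms into the estimate.

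Age acts in the same direction and may differ between arms for two reasons. One is chance, with communities allocated by simple randomization. The other is the questionnaire rule in Data collection. In a sentence about the control group, it restricts completion to the youngest where a family has two children in the age range. No matching rule is stated for the intervention group, where Setting and participants foresees two children from one family. If the rule is applied only in the control group, control children would be systematically younger.

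**Working it through.** **No figure to reproduce.** Sample size calculation states that no formal calculation was done and gives 600 families. The article gives no significance level, ICC or number of communities. Everything below other than the 600 families and the drunkenness percentages is assumed.

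**1. Type I error if ordinary tests were run.** Assume equal-sized communities, one child per family and a two-sided 5% test. With m families per community:

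- Design effect: DE = 1 + (m − 1) × ICC
- True type I error: 2 × [1 − Φ(1.96/√DE)]

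| Communities (m) | ICC 0.01 | ICC 0.02 | ICC 0.05 |
|---|---|---|---|
| 40 (15) | DE 1.14, 6.6% | DE 1.28, 8.3% | DE 1.70, 13.3% |
| 30 (20) | DE 1.19, 7.2% | DE 1.38, 9.5% | DE 1.95, 16.0% |
| 20 (30) | DE 1.29, 8.4% | DE 1.58, 11.9% | DE 2.45, 21.1% |

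Worst corner: DE = 1 + 29 × 0.05 = 2.45; 1.96/√2.45 = 1.25; two-sided tail about 21%.

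**2. What an age difference could do.** A straight line through the two Background figures gives (53 − 10)/(15 − 11) = 10.75 percentage points of ever having been drunk per year of age.

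To see how large a chance difference might be, assume ages uniform over 10 to 14 (SD 1.41) and 300 children per arm. With independent children the standard error of the difference in mean age is 1.41 × √(2/300) = 0.115 years.

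- With DE 2.45: 0.115 × √2.45 = 0.18 years. A 1.96-SE difference is about 0.35 years, and 0.35 × 10.75 is about 4 points.
- With a strong assumed age ICC of 0.20 and m = 30: DE = 1 + 29 × 0.20 = 6.8, and the standard error is 0.115 × √6.8 = 0.30 years. A 1.96-SE difference is about 0.59 years, or about 6 points.

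A full one-year difference would be more than 5 standard errors in the first case and more than 3 in the second, so chance is unlikely to produce it. A quarter-year difference, from whatever source, would be worth 0.25 × 10.75 = about 2.7 points. The size of any systematic difference from the youngest-child rule cannot be computed, because the article does not say how many families have two children in the age range.

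**3. Precision from baseline adjustment.** For a continuous outcome with independent observations, adjustment multiplies the residual variance by 1 − r², where r is the correlation between baseline and follow-up. At assumed r of 0.3, 0.5 and 0.7 this gives 0.91, 0.75 and 0.51. At r = 0.5 the gain equals 1/0.75 − 1 = 33% more families.

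This only indicates the direction. The primary outcomes are mainly binary, and covariates in a logistic model do not shrink the variance of the log odds ratio by 1 − r². In a cluster trial the gain also depends on separate within-community and between-community correlations.

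**The case against.** The strongest reply is that clustering is already covered. The section opens by committing to multi-level analysis, and the next sentence can be read as naming the type of contrast, proportions or means, inside that framework. A two-sample or rank test on community-level summaries would also be valid in a cluster trial. This largely stands. A reader might infer that the trial will ignore clustering, or that the two sentences contradict each other. The text supports neither: it never says that children are treated as independent, and the inflated error rates arise only if the opening commitment is set aside.

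A reader might also infer that the comparison is unadjusted, uses follow-up values only, or throws away baseline and age. The article says none of this. It is silent on covariates, a full covariate list is commonly left to a fuller document, and age does enter through the sub-groups. What remains is that the article does state a comparison method, that this method as worded has no place for baseline or age, and that a sub-group split does not adjust the whole-sample comparison.

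Finally, chance imbalance is not bias. A correct cluster-level standard error already allows for it, and omitting covariates does not by itself invalidate a randomized comparison. That is right for chance differences. It does not cover a systematic age difference caused by a child-selection rule applied in one arm only.

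**Conclusion.** The point holds as an unreconciled ambiguity together with a weaker choice of comparison than the data allow. The article does not show that the primary test will be invalid.

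The clustering part matters more because it governs type I error: about 6.6% to 21% in place of 5%, conditional on ordinary tests being used, on 15 to 30 families per community and on an ICC of 0.01 to 0.05, all of which are assumed.

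The covariate part concerns precision and age differences left in the estimate. Under the assumptions shown, a chance age difference could plausibly be worth up to about 4 to 6 percentage points on ever having been drunk, taking the age gradient as linear. The precision gain from adjustment is real in direction but of unknown size here. Any systematic age difference depends on how the youngest-child rule is applied in the intervention arm, which the article leaves open.

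**What to change.** Replace the test sentence in Analyses with one primary cluster-adjusted comparison per outcome type:

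- a mixed-effects logistic model for binary outcomes and a mixed-effects linear model for continuous outcomes;
- a random effect for community, and for family where more than one child is analysed;
- fixed effects for arm, the baseline value of the outcome where it is measured, and child age;
- a small-sample correction based on the number of communities, for example Kenward–Roger or Satterthwaite for linear models, or a t reference with communities minus 2 degrees of freedom.

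Keep plain or rank tests only for community-level summaries or as a sensitivity analysis. State also whether the youngest-child rule applies in both arms; an age term helps with a difference in measured age but does not replace a common selection rule.

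The cost is small. Baseline data are already collected and child age already defines a sub-group, so only the analysis wording changes. There is slightly more modelling work, and the logistic model gives a conditional odds ratio, which can be reported together with a marginal risk difference.

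### The stated subgroup method tests the arms within each stratum and names no arm-by-subgroup interaction, so as written it cannot show whether the effect differs

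*Protocol article*

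**What the plan says.** The protocol article, under Analyses, names its inferential method: "Statistical tests of difference in proportions or mean difference tests (or non-parametric equivalents) will be used to examine differences between intervention and control groups". The following sentence says that "data will be analyzed for the whole sample and by several sub-group analyses". Three factors are listed, each with two levels: child age (10 to 12 against 13 to 14 years), "family problems (violence, chronic illness, substance use problems, financial problems etc.; low vs high severity"), and "child behaviour and emotional problems (low vs high severity"). They are named in advance and attributed to pilot results. The section also says "Clustering at the community and family level will be taken account of in multi-level data analysis".

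No arm-by-subgroup interaction is mentioned, and no rule is given for reading subgroup results. Stratum sizes and severity cut-offs are not given. Under Sample size calculation, the article says "No formal sample size calculation was undertaken but funding was requested for a sample size (N = 600 families").

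**The concern.** The natural reading is that the same comparison of arms is run once in the whole sample and again inside each level of each factor. Each stratum test asks whether there is an effect in that stratum. None asks whether the effect differs from that in the other stratum. A significant result in one level and a non-significant result in the other is a common pattern when the effect is identical in both, because each stratum has fewer families and so less power.

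Subgroups are of interest here precisely because the programme might work differently by age or by level of family or child problems. If the answer is read from stratum p-values, a uniform effect can look as if it were confined to one kind of family. The risk is not limited by design, since the 600 families were not derived from a power calculation and power within strata is unknown.

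**Working it through.** The plan gives no significance level, power, effect size, intracluster correlation or stratum share, so there is no stated figure to reproduce. The inputs below are assumptions, shown over a range.

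**Inputs.** From the article: three two-level factors, communities as the unit of randomization, 1:1 allocation. Assumed: two-sided 5% tests, approximately normal test statistics, the same true effect in both strata, strata split 50/50 or 30/70, overall power 30% to 90% or a null effect.

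**Step 1. Independent strata.** Let δ = 1.96 + Φ⁻¹(overall power), or 0 under the null. A stratum holding share f of the information has power Φ(δ√f − 1.96) + Φ(−δ√f − 1.96). With powers a and b in the two strata, P(exactly one significant) = a(1 − b) + b(1 − a).

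- 80% overall power, 50/50 split: δ = 2.80, δ√0.5 = 1.98, stratum power 0.508. Discordance = 2 × 0.508 × 0.492 = 0.50.
- 80% overall power, 30/70 split: powers 0.335 and 0.650. Discordance = 0.335 × 0.350 + 0.650 × 0.665 = 0.55.
- Null effect: 2 × 0.05 × 0.95 = 0.095.

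The chance that at least one of three factors shows this pattern comes from simulation (200,000 runs, three independent crossed factors, eight cells).

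| Overall power | Exactly one stratum significant, one factor | At least one of three factors |
|---|---|---|
| Null effect | 9.5% | 21% |
| 30% | 29% | 48% to 49% |
| 50% | 41% to 42% | 64% to 65% |
| 80% | 50% to 55% | 75% to 81% |
| 90% | 47% to 54% | 71% to 82% |

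**Step 2. Strata that share communities.** Step 1 treats strata as independent. If both levels of a factor occur in each community, the two stratum estimates share the community effect. With m families per community, intracluster correlation ρ and an even split within communities:

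- variance of the overall estimate is proportional to V = ρ + (1 − ρ)/m;
- variance of a stratum estimate is proportional to Vs = ρ + 2(1 − ρ)/m;
- correlation between the two stratum estimates is ρ/Vs;
- the mean of the stratum test statistic is δ√(V/Vs).

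At 80% overall power (m and ρ assumed), discordance follows from the bivariate normal distribution:

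| m | ρ | V/Vs | Correlation | Stratum power | Exactly one significant |
|---|---|---|---|---|---|
| 15 | 0.01 | 0.076/0.142 = 0.535 | 0.07 | 54% | 48% |
| 15 | 0.10 | 0.16/0.22 = 0.727 | 0.45 | 67% | 32% |
| 30 | 0.01 | 0.043/0.076 = 0.566 | 0.13 | 56% | 45% |
| 30 | 0.10 | 0.13/0.16 = 0.813 | 0.63 | 71% | 24% |

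Under a null effect, the any-of-three figure falls from 21% to about 18% (m = 15, ρ = 0.05) or 16% (m = 30, ρ = 0.05). Simulating the same model at m = 30, ρ = 0.10 gives about 13%.

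**Step 3. Interaction tests.** One 5% interaction test per factor has a 5% chance of falsely declaring a difference, whatever the overall effect. For three factors, 1 − 0.95³ = 14.3%; the Step 1 simulation gave 14.1% to 14.3% in every scenario. In the Step 2 model the shared community effect cancels from the contrast between strata.

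**The case against.** The strongest objection is that the missing interaction is inferred from silence. This is a condensed article with a one-paragraph Analyses section. The multi-level model can hold an interaction term, and an analysis plan that is not shown may specify one. That stands against any statement that the authors rejected interaction tests. It does not dispose of the point, because the article does more than omit a detail: it names the test and the strata to which it is applied, and that combination does not answer a question about effect modification.

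Other stronger readings are tempting, and the documents do not support them.

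- A reader might infer that a claim of benefit in one subgroup only is planned. The article says no such thing. Its aims and Discussion concern overall effectiveness and transferability, and the subgroups are few and named in advance.
- A reader might call a spurious subgroup finding likely by chance. With no effect at all, the split pattern has a probability of about 10% per factor and at most about 21% for any of three on one outcome. Interaction tests still leave about 14%, and under strong clustering the null comparison shows little or no difference. The substantial gap arises when the effect is real and uniform.
- A reader might speak of halves. Each factor has two levels, but their shares are not stated.
- A reader might multiply out the tests. Counting 4 + 4 + 3 + 1 + 1 = 13 primary measures, 13 × 6 strata × 2 follow-ups = 156 tests, and 5% of these is 7.8. That expectation needs no effect on any measure at either follow-up, and it counts age of first use twice although it is not a per-visit measure.

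The objection that independent strata overstate the discordance also stands, and Step 2 allows for it.

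**Conclusion.** The point holds in a limited form. The analysis as described yields stratum-wise p-values that cannot establish a differential effect, and the article names nothing that could. The size depends on what is true. With a uniform real effect, the misleading split is common: roughly one case in four to one in two per factor and outcome under most of the assumptions tried, with the lower end reached when communities are large, strongly clustered and mixed in stratum. With no effect, the excess over interaction testing is modest and can vanish. These figures rest on assumed power, stratum shares, intracluster correlation and community size, none of which the article gives. The conclusion that stratum p-values cannot show effect modification needs none of these assumptions.

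**What to change.** Add to the Analyses section, or confirm in the analysis plan, that:

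1. differences in effect between subgroups are judged by an arm-by-subgroup interaction term in the planned multi-level model;
2. stratum-specific estimates are shown with confidence intervals and labelled exploratory;
3. no conclusion that the effect differs is drawn from stratum p-values alone.

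Even a significant interaction should be read with the roughly 14% chance of at least one false positive over three factors in mind. Entering age as a continuous moderator is optional: it uses more information than two age bands but assumes a form, usually linear, for how the effect changes with age. The same cannot be required for family problems, since the article describes no continuous score for them. The change does not depend on choosing a single primary outcome or time point.

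The cost is a few sentences and no new data. The drawback is that interaction tests have low power, so fewer subgroup claims can be made and a non-significant interaction will not show that effects are equal.
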